**Secondary outcome variables**

- Knowledge, attitudes, and control towards IPV during pregnancy
- Knowledge: Good versus Poor Knowledge,
- Attitude: supportive versus not supportive attitude toward IPV
- Controlling behavior: yes versus no
- Women’s autonomy and self-efficacy

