**Controlling behavior**: couples will be asked six questions: (i) “jealous if she talked with other men”, (ii) ”accused her of unfaithfulness”, (iii) “did not permit her to meet her friends,(iv) “tried to limit her contact with family,(v) “insisted on knowing where she is, and “did not trust her with money(Antai, 2011). Couples responded “yes” to one or more of the control questions coded as 1. Otherwise, it will be coded 'no as 0.

**Women’s autonomy**: women's decision-making Autonomy will be assessed by asking couples who decide on household purchases, including small and large ones, and who decides on visiting relatives and friends. Who decides how to spend the wife's earnings? Who decides the number of children to have? And who decides to obtain health care for themselves? The response options will be “husband only’’, wife only’’ or ‘’both husband and wife”. Women will be considered to participate in decision-making if they make decisions alone or jointly with their husbands. A composite measure will be created using the sums of equally weighted binary input variables. Women will be scored one (1) for answers to each variable that included her (alone or jointly) in decision-making; otherwise, they will be scored zero (0). The index of household decision-making power (autonomy) contains five variables; thus, the respondents will be scored from 0 to 5. Two binary measures from these indexes will be created to indicate women with higher versus lower autonomy. The high and low categories will be created by dividing the sample indexes into approximately half, in which those who score below the mean score are considered to have low autonomy or lower involvement in household decision-making, and those who score above the mean score are considered to have higher decision-making autonomy or higher involvement in household decision-making (Uthman et al., 2009).

**Women’s Self-Efficacy: The** Generalized Self-Efficacy Scale (GSES), which was developed by Albert Bandura, will be used. The General Self-Efficiency Scale (GSES) consists of 10 items scored on a 4-point Likert scale, from 1 (not at all true) to 4 (exactly true). The total scale ranges from 10 to 40, with higher self-efficacy (score of ≥20) and lower self-efficacy (score of <20) (Liping Peng et al., 2020).

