**6.21 Data collection instruments**

**Questionnaires**

**Quantitative study**: structured-interviewer-administered questionnaires adapted from the WHO multi-country study questionnaire will be used to collect information on intimate partner violence in pregnancy (WHO, 2010). The English version of the questionnaire will be translated into the local language (Hadiyisa) by fluent speakers. Then, the questionnaire's local language will be translated back to English by another expert to ensure consistency and accuracy. Four types of questionnaires will be administered at baseline and at the endline for couples (pregnant wife and husband). The data will be collected using a mobile-based application called KoBo Collect. The content of the information under each questionnaire will be as follows:

**Questionnaire for pregnant mothers at baseline and end-line**: the questionnaire will be administered to all pregnant women in the two groups (intervention and control groups) after obtaining informed verbal and written consent. The questionnaire contains individual characteristics of mothers, including age, levels of education, occupation, marriage type, parity, pregnancy intention, and household characteristics. Relational characteristics: duration of marriage and disparity in educational attainment

Moreover, the relational characteristics include the presence of social support and religion. The societal characteristics of pregnant women include women’s autonomy in addition to male involvement in antenatal care. All questionnaires will be administered to the intervention and control groups before any education session. Outcome measures: couples' knowledge, attitude, and control towards IPV; self-efficacy; pregnant women’s experience of IPV in the last 12 months and during the recent pregnancy

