|  | Who makes Final decisions in your household activities :  1. wife alone  2. Respondent and husband together  3. Husband alone  4. someone else | | | |  | | | | | | | | | | | | | | |  | | |
| 501 | On household purchases including small and large ones? | | | | 1 | | | | 2 | | | | | 3 | | | | 4 | |  | | |
| 502 | Visiting relatives and friends? | | | | 1 | | | | 2 | | | | | 3 | | | | 4 | |  | | |
| 503 | Spending the wife's earnings? | | | | 1 | | | | 2 | | | | | 3 | | | | 4 | |  | | |
| 504 | The number of children to have? | | | | 1 | | | | 2 | | | | | 3 | | | | 4 | |  | | |
| 505 | Obtaining health care for you? | | | | 1 | | | | 2 | | | | | 3 | | | | 4 | |  | | |
| 506 | **SOCIAL SUPPORT** | | | | | | | | | | | | | | | | | | |  | | |
| 507 | How many people are so close to you that you can count on them if you have great personal problems? | | | | None...................................................1  1–2.....................................................2  3–5.....................................................3  5+......................................................4 | | | | | | | | | | | | | | |  | | |
| 508 | How much interest and concern do people show in what you do? | | | | none…………………………………1  little………………………..………...2  uncertain…………….........…………3  some………………….……………..4  a lot………………….………………5 | | | | | | | | | | | | | | |  | | |
| 509 | How easy is it to get practical help from neighbors if you should need it? | | | | very difficult …...………………..…1  difficult…………..…………………2  possible…………………..…………3  Easy…………………….………..…4  very easy…..….…………….………5 | | | | | | | | | | | | | | |  | | |
|  | **PART SIX: KNOWLEDGE, ATTITUDE AND CONTROLLING BEHAVIOUR QUESTIONS** | | | | | | | | | | | | | | | | | | |  | | |
| 600 | **Knowledge** | | | | | | | | | | | | | | | | | | |  | | |
| 601 | Have you heard of Intimate partner violence? | | | | 1. Yes 2. No | | | | | | | | | | | | | | |  | | |
| 602 | Media, hospitals, health center are examples of sources of information for intimate partner violence | | | | Yes ----------------------------------1  No -----------------------------------2 | | | | | | | | | | | | | | |  | | |
| 603 | IPV is a serious public health issue | | | | Yes ………………………………….1  No …………………………………..2 | | | | | | | | | | | | | | |  | | |
| 604 | Slapping, kicking, dragging, beating, choking, pushing, etc., are examples of IPV | | | | Yes…………………………………..1  No …………………………………..2 | | | | | | | | | | | | | | |  | | |

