| 500 | **የሴቶች በራሳቸዉ የመወሰን መጠይቅ** | | | | | | | | | | | |  |
|  | በሚከተሉት የቤት ዉስጥ ጉዳዮች ላይ የመጨራሻ ዉሳኔ ሰጪማን ነዉ?  1.ሚስትብቻ 2. ባልብቻ 3. ባልና ምስት አንድላይ 4 ሌላ ሰዉ/ የቤተብ አባል | | |  | | | | | | | | |  |
| 501 | ትናንሽ እና ትላልቅ ግዢዎችን ጨምሮ በቤተሰብ ግዢዎች ላይ? | | | 1 | 2 | | 3 | | | | 4 | |  |
| 502 | ዘመዶችን እና ጓደኞችን ለመጎበኛት? | | | 1 | 2 | | 3 | | | | 4 | |  |
| 503 | የሚስቱን ገቢ ወጪ በማድረግ? | | | 1 | 2 | | 3 | | | | 4 | |  |
| 504 | የሚወልዱ ልጆች ብዛት? | | | 1 | 2 | | 3 | | | | 4 | |  |
| 505 | ለእርስዎ የጤና እንክብካቤ ለማገኘት? | | | 1 | 2 | | 3 | | | | 4 | |  |
| 506 | **ማህበራዊ ድጋፍ** | | | | | | | | | | | |  |
| 507 | ምን ያህል ሰዎች ከእርስዎ ጋር በጣም ቅርብ ስለሆኑ ታላቅ የግል ችግሮች ካጋጠሙዎት በእነሱ ላይ መተማመን ይችላሉ? | | | የለም...................................................1  1–2.....................................................2  3–5.....................................................3  5+......................................................4 | | | | | | | | |  |
| 508 | ሰዎች በምታደርገው ነገር ምን ያህል ፍላጎት እና አሳቢነት ያሳያሉ? | | | ምንም………………………………1  ትንሽ……………………..……...…...2  እርግጠኛ አይደለሁም...........…………3  የተወነ……………….…………...…..4  ብዙ………………….………………5 | | | | | | | | |  |
| 509 | ከፈለጉ ከጎረቤቶች ተግባራዊ እርዳታ ማግኘት ምን ያህል ቀላል ነው? | | | በጣም ከባድ …...………………..…1  ከባድ…………..………….…………2  ይቻላል…………………..…..………3  ቀላል…………………….………...…4  በጣም ቀላል…..….………….………5 | | | | | | | | |  |
|  | **ክፍል ስድስት : የእውቀት፣ የአመለካከት እና የባህሪ መቆጣተር ጥያቄዎች** | | | | | | | | | | | |  |
| 600 | **እዉቀት** | | | | | | | | | | | |  |
| 601 | ስለ የቅርብ አጋር ጥቃት ሰምተዉ ያዉቃሉ? | | | አዎ ……………………….1  አላዉቅም----------------2 | | | | | | | | |  |
| 602 | የቅርብ አጋር ጥቃት ላይ የመረጃ ምንጮች ሚዲያ፣ሆስፕታል፣ጤና ጣቢያ ፣ጤና ጣቢያ ወዘተ..ናቸዉ? | | | አዎ ……………………….1  አላዉቅም----------------2 | | | | | | | | |  |
| 603 | የቅርብ አጋር( ጥቃት የህዝብ ጤና ጉዳይ ነው። | | | አዎ ………………………………….1  አይደለም……………..……………..2 | | | | | | | | |  |
| 604 | በጥፊ መምታት፣ መምታት፣ መጎተት፣ መደብደብ፣ ማነቅ፣ መግፋት፣ ወዘተ.የፍቅር አጋር ጥቃት ምሳሌዎች ናቸው። | | | አዎ ………………………………….1  አይደለም……………..……………..2 | | | | | | | | |  |
| 605 | ባልፈለገች ጊዜ ወሲብ እንዲፈጽም ማስገደድ ወሲባዊ ጥቃት ነው። | | | አዎ ………………………………….1  አይደለም……………..……………..2 | | | | | | | | |  |
| 606 | እሱ/እሷ የሚያዋርድ ወይም የሚያዋርድ ነገር እንዲፈጽም ማስገደድ ወሲባዊ ጥቃት ነው። | | | አዎ ………………………………….1  አይደለም……………..……………..2 | | | | | | | | |  |
| 607 | አጋርን በሌሎች ሰዎች ፊት ማዋረድ ወይም ማዋረድ የስነ-ልቦና ጥቃት ነው። | | | አዎ ………………………………….1  አይደለም……………..……………..2 | | | | | | | | |  |
| 608 | በእርግዝና ወቅት የቅርብ ወዳጃዊ ጥቃት የእናቶች እና አዲስ የሚወለዱ ሕፃናት ላይ አሉታዊ ውጤቶች አሉት፡፡ | | | አዎ ………………………………….1  አይደለም……………..……………..2 | | | | | | | | |  |

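### Answer codes 2 and 3 of the women's autonomy items are interchanged between the English and Amharic forms, so scoring one form's codes by the other form's key would mis-score joint and husband-alone decisions

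*Protocol*

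**What the plan says.** Annex II, Part Five (English form, items 501-505) asks who makes the final decision on five household matters. Code 1 is the wife alone, then "2. Respondent and husband together", then "3. Husband alone"; code 4 is someone else.

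Annex VI (Amharic form, items 501-505) asks about the same five matters with this key: "1.ሚስትብቻ 2. ባልብቻ 3. ባልና ምስት አንድላይ 4 ሌላ ሰዉ/ የቤተብ አባል". In English: 1 wife only, 2 husband only, 3 husband and wife together, 4 another person or family member.

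Section 6.17, Women's autonomy, sets the scoring: "Women will be scored one (1) for answers to each variable that included her (alone or jointly) in decision-making", otherwise zero. The five items are summed, "thus, the respondents will be scored from 0 to 5", and the index is split at the sample mean into lower and higher autonomy. The section gives no code numbers and lists the answer options in a third order: husband only, wife only, both.

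Section 6.6.1 lists "Women’s autonomy and self-efficacy" among the secondary outcomes, and specific objective 5 is about them. On language, section 6.21 states: "The English version of the questionnaire will be translated into the local language (Hadiyisa) by fluent speakers". Section 6.16 also names Hadiyisa, while section 6.22 speaks of an Amharic version. Data are captured in KoBo Collect and exported to SPSS or STATA (sections 6.21 and 6.24).

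**The concern.** The two codes that change places lie on opposite sides of the scoring rule: a joint decision earns the point and a husband-alone decision does not. A swap of wife-alone and joint would have done no harm, because both earn the point.

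The swap also falls where an effect would be expected. The session schedule in the trainers' manual and Table 2 put the benefits of joint decision-making, and strategies for it, in session 5. A change from husband-alone to joint decisions is therefore one that the education aims at. Scored by the wrong key, that change would count against the intervention and could turn the direction of the autonomy result.

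**Working it through.** The protocol states no figure to reproduce, so the check compares the two code lists under the scoring rule and then illustrates the size.

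**Step 1. Apply the rule (wife alone or jointly = 1, otherwise 0) to each code.**

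| Code | English form | Score | Amharic form | Score | Agree? |
|---|---|---|---|---|---|
| 1 | wife alone | 1 | wife only | 1 | yes |
| 2 | together | 1 | husband only | 0 | **no** |
| 3 | husband alone | 0 | together | 1 | **no** |
| 4 | someone else | 0 | other person | 0 | yes |

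By the English key, codes 1 and 2 earn the point. By the Amharic key, codes 1 and 3 do. Scoring either form by the other's key produces the same error: joint answers get 0 and husband-alone answers get 1. With one list on both forms, no item is mis-scored.

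**Step 2. Item-level size.** Let *w*, *j* and *h* be the shares of wife-alone, joint and husband-alone answers.

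- True participation: T = *w* + *j*
- Mis-scored participation: F = *w* + *h*

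Assume *w* = 15%, *j* = 60%, *h* = 25%. Then T = 15 + 60 = 75% and F = 15 + 25 = 40%. Now move 15 points from husband-alone to joint (*j* = 75%, *h* = 10%). T becomes 90%, a rise of 15 points. F becomes 25%, a fall of 15 points.

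If only a share *q* of answers is scored by the wrong key, the same in both arms, a true shift *d* from husband-alone to joint appears as (1 − *q*)*d* − *q d* = (1 − 2*q*)*d*. It vanishes at *q* = 1/2 and changes sign above that.

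**Step 3. The 0-5 index.** Assume that the five items are independent with the same answer shares. The true mean is 5T and the mis-scored mean is 5F. The correlation between the two indices is (*w* − TF) / √[T(1 − T)F(1 − F)]. The answer shares below are assumptions; the protocol gives none.

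| Wife / joint / husband / other | True mean | Mis-scored mean | Correlation | In the wrong high/low class |
|---|---|---|---|---|
| 10 / 50 / 35 / 5% | 3.00 | 2.25 | −0.70 | 79% |
| 15 / 60 / 20 / 5% | 3.75 | 1.75 | −0.54 | 68% |
| 30 / 40 / 25 / 5% | 3.50 | 2.75 | −0.37 | 63% |
| 0 / 60 / 40 / 0% | 3.00 | 2.00 | −1 | see below |

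First row: (0.10 − 0.60 × 0.45) / √(0.60 × 0.40 × 0.45 × 0.55) = −0.17 / 0.244 = −0.70.

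Section 6.17 classes scores below and above the mean but not scores equal to it. In the first row the true mean is exactly 3: the 79% counts a score of 3 as high, and counting it as low gives 68%. In the last row both means are whole numbers, so the misclassified share depends on the same choice and only the correlation is quoted.

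**The case against.** The strongest reply is that section 6.17 scores answers by meaning and not by number. Followed as written, with each form read by its own key, it scores both forms correctly. No section says that English codes will be applied to Amharic forms. The KoBo code list is not shown, and the annex numbering need not be what is stored. All this stands, and it makes the harm conditional.

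A reader might infer that either key reverses the whole autonomy outcome. The documents do not support that. Two of the four codes score the same under both keys, and the index is an exact mirror image only if every answer is joint or husband-alone. In the example in step 2, a true reversal of 75% would give 25%, not 40%. Nor do the documents show that mis-scoring will occur, or that it could reach the primary outcome, which rests on other items.

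The link to the education content is also looser than the schedule suggests: the manual's step-by-step text for session 5 is titled as triggers of violence and does not list joint decision-making.

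Sections 6.16 and 6.22 plan back-translation, item-by-item comparison, an expert committee, a pilot with 27 couples and a pre-test. These lower the risk. They are aimed at wording and interpretation, however, and would not clearly catch a reordered option list whose labels are each translated correctly. Data collectors must speak both languages and the Amharic form is the translation annexed, so its use cannot be ruled out.

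**Conclusion.** The two annexed forms contradict each other on codes 2 and 3 of items 501-505, and nothing in the protocol says which key governs. If numeric codes from one form are scored by the other's key, or the two forms are pooled uncorrected, every joint answer scored by the wrong key loses its point and every husband-alone answer gains one. A woman with five joint decisions would score 0 instead of 5, and a real move from husband-alone to joint decisions could appear as a fall.

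The percentages rest on assumed answer shares and, for the index, on independent items; they show the mechanism and do not forecast an effect. The point concerns one secondary outcome. It should be put right before scoring because the direction of that result depends on it.

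**What to change.** Use one code list for items 501-505 in the English, Amharic and Hadiyisa versions and in the KoBo form, for example 1 wife alone, 2 both, 3 husband alone, 4 someone else. In section 6.17, tie the point to the response labels or to that list by number. If any data have already been collected on the Amharic form, confirm the stored code mapping before the index is computed. The cost is one correction to the forms and one scoring check; the design, the sample size and the primary analysis do not change.

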**5.3.2 Specific Objectives**

1. To assess the prevalence and associated factors of IPV during pregnancy
2. To explore the community's perspectives of IPV during pregnancy
3. To evaluate the effect of couple-based violence prevention education on couples knowledge, attitudes, and controlling behavior towards IPV during pregnancy
4. To compare the effect of couple-based violence prevention education on the experience of IPV during pregnancy
5. To compare the effect of couple-based violence prevention education on women’s autonomy and self-efficacy

1. **Methods and Materials**

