**Emotional/psychological violence: a** pregnant mother will be asked the following three psychological violence questions: (i) “say or do something to humiliate her in front of another person”, (ii) "threat to hurt or harm her or someone she cares about,” and (iii) insult or make her feel bad about herself” in the last 12 months and during the most recent pregnancy (Abramsky et al., 2011). If the mother responds to one of these emotional or psychological IPV questions, it will be recorded as 1 = yes; otherwise, 0=no (she has not experienced any emotional or psychological intimate partner violence during this pregnancy).

**Social support: The** Oslo-3 Social Support Scale (OSSS-3) will be used to measure the social support of women. The OSSS-3 consists of three items assessing the level of social support among women. Pregnant women will be asked, **Oslo 1**: How many people are so close to you that you can count on them if you have great personal problems? The responses will be: 1. 'None, 2. ‘1–2’ 3. ‘3–5’ 4, ‘5+’; **Oslo 2:** How much interest and concern do people show in what you do? The responses will be "none."2 ‘little’ 3 ‘uncertain’ 4 ‘some’ 5 ‘a lot’ and **Oslo 3**: How easy is it to get practical help from neighbors if you should need it? The response will be 'very difficult. 2 ‘difficult’ 3 ‘possible’ 4 ‘easy’ 5'very easy. The sum scores range from 3 to 14. Then the sum scores will be categorized as 3–8 (**poor social support**), 9–11 (moderate**social support),** and 12–14 (strong**social support**).

**Knowledge of IPV:** couples will be asked about nine items of knowledge questions on IPV. Couples who scored about 75% or above of the correct answer will be scored as “good knowledge,” and those who scored less than 75% will be scored as “poor knowledge (Oche et al., 2020).

**Attitude towards IPV**: To measure attitude toward intimate partner violence during pregnancy, couples will be asked, “In your opinion, is a husband justified in hitting or beating his wife in the following situations?" (a) “If she goes out without telling him?” (b) “If she neglects the children?” (c) “If she argues with him?” (d) “If she refuses to have sex with him?” (e) “If she burns the food?” Responses of “supportive attitude toward IPVp” to one or more of the scenarios were coded 1; “not supportive attitude toward IPVp" to all scenarios was coded '0'. (Trott et al., 2017).

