| 605 | Forcing partner to have sex when he/she does not want to is sexual violence | | | | Yes………………………………….1  No…………………………………..2 | | | | | | | | | | | | | | |  | | |
| 606 | Forcing partner to do something sexual that he/she finds degrading or humiliating is sexual violence | | | | Yes………………………………….1  No………………………..………….2 | | | | | | | | | | | | | | |  | | |
| 607 | Belittling or humiliating a partner in front of other people is psychological violence | | | | Yes……………………………….….1  No…………………………………...2 | | | | | | | | | | | | | | |  | | |
| 608 | Intimate partner violence during pregnancy has adverse maternal and newborn outcomes | | | | Yes…………………………….…….1  No…………………………………...2 | | | | | | | | | | | | | | |  | | |
| 609 | Intimate partner violence is human right violation | | | | Yes……………………………….….1  No…………………………………...2 | | | | | | | | | | | | | | |  | | |
| 610 | **Attitude** | | | | | | | | | | | | | | | | | | |  | | |
| 611 | In your opinion, is a husband justified in hitting or beating his wife in the following situation   1. Yes 2. No | | | | | |  | | | | | | | | | | | | |  | | |
| 612 | If she goes out without telling him? | | | | | | 1 | | | | | | | | | | 2 | | |  | | |
| 613 | If she neglects the children? | | | | | | 1 | | | | | | | | | | 2 | | |  |  |  |
| 614 | If she argues with him? | | | | | | 1 | | | | | | | | | | 2 | | |  |  |  |
| 615 | If she refuses to have sex with him? | | | | | | 1 | | | | | | | | | | 2 | | |  |  |  |
| 616 | If she burns the food? | | | | | | 1 | | | | | | | | | | 2 | | |  |  |  |
| 617 | **Controlling behavior** | | | | | | | | | | | | | | | | | | |  |  |  |
|  | In your opinion, is the husband is justified in controlling you in the following situation?   1. Yes 2. No | | | | | | | | | | | | | | | | | | |  |  |  |
| 618 | Jealous if she talked with other men | | | | | | 1 | | | | | | 2 | | | | | | |  | | |
| 619 | Accused her of unfaithfulness | | | | | | 1 | | | | | | 2 | | | | | | |  |  |  |
| 620 | Did not permit her to meet her friends | | | | | | 1 | | | | | | 2 | | | | | | |  | | |
| 621 | Tried to limit her contact with family | | | | | | 1 | | | | | | 2 | | | | | | |  |  |  |
| 622 | insisted on knowing where she is | | | | | | 1 | | | | | 2 | | | | | | | |  | | |
| 623 | did not trust her with money | | | | | | 1 | | | | | 2 | | | | | | | |  |  |  |

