| 204 | Slapping, kicking, dragging, beating, choking, pushing, etc., are examples of IPV | | | Yes…………………………………..1  No …………………………………..2 | | | |  | |
| 205 | Forcing partner to have sex when he/she does not want to is sexual violence | | | Yes………………………………….1  No…………………………………..2 | | | |  | |
| 206 | Forcing partner to do something sexual that he/she finds degrading or humiliating is sexual violence | | | Yes………………………………….1  No………………………..………….2 | | | |  | |
| 207 | Belittling or humiliating a partner in front of other people is psychological violence | | | Yes……………………………….….1  No…………………………………...2 | | | |  | |
| 208 | Restricting a partner from contact with family or friends | | | Yes…………………………….…….1  No…………………………………...2 | | | |  | |
| 209 | Intimate partner violence is human right violation | | | Yes……………………………….….1  No…………………………………...2 | | | |  | |
| 210 | **Attitude** | | | | | | |  | |
|  | In your opinion, is a husband justified in hitting or beating his wife in the following situation?  1---------------Yes  2…………… No | | | | | | |  | |
| 211 | If she goes out without telling him? | Yes…………………………………….….…...1  No…………………………………….…….…2 | | | | | |  | |
| 212 | If she goes out without telling him? | Yes…………………………………….….…...1  No…………………………………….…….…2 | | | | | |  | |
| 213 | If she neglects the children? | Yes…………………………………….….…...1  No…………………………………….…….…2 | | | | | |  | |
| 214 | If she argues with him? | Yes…………………………………….….…...1  No…………………………………….…….…2 | | | | | |  | |
| 215 | If she refuses to have sex with him? | Yes…………………………………….….…...1  No…………………………………….…….…2 | | | | | |  | |
| 216 | **Controlling behavior** | | | | | | |  | |
|  | In your opinion, is the husband is justified in controlling his wife in the following  Situation? | | | | | |  | | |
| 217 | Jealous if she talked with other men | | | | 1 | 2 | |  | |
| 218 | Accused her of unfaithfulness | | | | 1 | 2 | |  |  |
| 219 | Did not permit her to meet her friends | | | | 1 | 2 | |  |  |
| 220 | Tried to limit her contact with family | | | | 1 | 2 | |  |  |
| 221 | insisted on knowing where she is | | | | 1 | 2 | |  |  |
| 222 | did not trust her with money | | | | 1 | 2 | |  |  |
|  | **PART THREE: Male Involvement in maternal health care (MHC)** | | | | | | |  | |
| 301 | Did your wife take ANC during her recent pregnancy at health facility? | Yes………………………………………..…...1  No……………………………………….….…2 | | | | | |  | |

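### Controlling behaviour is collected as an opinion on whether control is justified, so the behavioural part of objective 3 cannot be answered as written

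*Protocol*

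**What the plan says.** Specific objective 3 (section 5.3.2) is to evaluate the effect on "couples knowledge, attitudes, and controlling behavior towards IPV during pregnancy", naming three things. Section 6.6.1 follows it with two separate binary secondary outcomes: "Attitude: supportive versus not supportive attitude toward IPV" and "Controlling behavior: yes versus no".

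Section 6.17 describes controlling behaviour through six items worded as things the husband does: being jealous, accusing her of unfaithfulness, keeping her from friends, limiting family contact, insisting on knowing where she is, and not trusting her with money. A respondent who says yes "to one or more of the control questions coded as 1" is counted as positive, otherwise 0. No opinion stem appears there.

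The annexed forms do carry one. The wives' English form (Annex II, Part Six) introduces the six items with "In your opinion, is the husband is justified in controlling you in the following situation". The husbands' English form (Annex III, items 217-222) asks the same about his wife, and the Amharic forms (Annexes VI and VII) use the same opinion stem.

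The forms are given at baseline and endline (section 6.21), and binary outcomes are compared before and after within arm by the McNemar test (section 6.24).

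**The concern.** An outcome reported as controlling behaviour, yes or no, will be read as what husbands did. The forms ask what respondents find justified. The sessions teach power and control in relationships and ways to challenge inequitable gender norms, so stated opinion could move in the intervention arm with no change in conduct at home. A fall would then be published as less controlling behaviour. No analysis can repair this afterwards, because the acts are not recorded anywhere else.

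**Working it through.** No arithmetic applies, and the plan states no figure to reproduce. The check sets the definition beside the instruments and then looks for any other item that could supply the behaviour.

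**1. Definition against forms**

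| Place | What it fixes |
|---|---|
| Objective 3, section 5.3.2 | Controlling behaviour named apart from attitudes |
| Section 6.6.1 | Own secondary outcome, yes/no; no acts listed |
| Section 6.17 | Six items worded as acts; any yes = 1; no stem and no recall window |
| Annex II, items 618-623 (wives, English) | Opinion stem: is control justified |
| Annex III, items 217-222 (husbands, English) | Same opinion stem |
| Annex VI, items 617-622 (wives, Amharic) | Same opinion stem |
| Annex VII, items 415-420 (husbands, Amharic) | Same opinion stem |

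**2. What a 1 means.** Applying the section 6.17 rule to the forms, a 1 means that the respondent finds the husband's control justified in at least one of six situations. The outcome name implies that the husband showed at least one of six behaviours. A woman can suffer all six and approve of none, scoring 0; another can suffer none and approve of one, scoring 1.

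**3. The stem matches the attitude block.** The stem has the same form as the attitude stem directly above it in Annex II, which asks whether hitting or beating is justified. Part Seven of Annex II, by contrast, asks what the partner did during the pregnancy. The experience format was therefore available and was used for the primary outcome.

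**4. Is the behaviour recorded elsewhere?**
- Part Seven covers physical, psychological and sexual acts, not the six control acts.
- The autonomy items (501-505) ask who makes the final decision, which is another outcome.
- Husbands' item 208 in Annex III, on restricting contact, sits in the knowledge block.

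No item records whether the husband did any of the six acts.

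**5. Attitude list (a separate, smaller point).** Section 6.17 defines five scenarios, the last being "If she burns the food". In Annex III, items 211 and 212 both read "If she goes out without telling him", and the burnt-food scenario is absent: five numbered items, four distinct scenarios. The Amharic husbands' form (items 410-414) and the wives' English form (items 612-616) have all five. Under an any-yes score, the husbands who could be misclassified are those who would approve only in the missing scenario; the document gives no figure for them.

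**The case against.** **The construct is loosely defined in the text.** Section 6.6.1 lists no acts, and its lead line speaks of control towards IPV alongside knowledge and attitudes. Section 6.17 supplies items but no stem. This stands in part: the act wording comes from section 6.17 alone. But an outcome named as behaviour, scored yes/no and listed next to attitude cannot fairly be read as a second opinion measure, and objective 3 separates the two as well.

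**The items keep past-tense act wording**, so some respondents may report events despite the stem. That is plausible. The result is a mixture of opinion and event with no way to tell them apart, which is still not a valid measure of behaviour.

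**Validation is planned.** Sections 6.16 and 6.22 provide for expert review, face and content validity, piloting in 27 couples and a pre-test with revision; section 6.22 names controlling behaviour among the scales to be tested. These steps might catch the stem, but none states a correction, and the same stem stands in all four forms.

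**Stronger readings that a reader might infer, and that the documents do not support:**
- That the trial asks the attitude outcome twice. The objects differ: one scale concerns beating, the other control. It is a second attitude scale, not a repeat.
- That the share of items affected (six of six, or one of five for husbands' attitude) measures bias. These are item counts and say nothing about how many respondents would be classified differently.
- That the missing husbands' item carries into the translations. The Amharic form has it. The Hadiyisa version is planned from the English but is not shown.
- That opinion is the measure most open to socially desirable answering. The documents offer no comparison, and asking a husband about his own controlling acts invites it too.

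**Conclusion.** The point holds. Section 6.17 and the four questionnaires disagree on what is measured. If the forms are used as they stand, opinion, or an inseparable mixture of opinion and event, is reported as behaviour, and the behavioural part of objective 3 goes unanswered. The defect is complete in extent (every item, both spouses, both languages shown) but confined to one secondary outcome. The primary IPV items use an experience stem and are not affected by this point. The size of any resulting error cannot be estimated from the document. The conclusion assumes that the annexed forms are the ones to be fielded and that no correction is made at pre-test.

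The husbands' attitude item is a copying slip in one form. It is worth correcting but carries little weight beside the main point.

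**What to change.** **If baseline has not been collected.** Replace the stem in Annexes II, III, VI and VII, and in the Hadiyisa version, with an experience stem that can be asked at both time points: for wives, the Part Seven form (during this pregnancy, did your partner...); for husbands, a matching did-you form. Keep the six acts and the any-yes rule, and report wives' and husbands' answers separately. State the same stem in section 6.17.

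State a recall window for each time point. A stem counting only from the baseline date cannot be asked at baseline, so baseline needs its own window. If endline asked about the whole pregnancy, a truthful yes at baseline would remain a yes, and the within-arm McNemar comparison could show no truthful fall; the endline window should be chosen with that in mind.

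**If baseline has been collected with the present stem.** Rename the outcome as attitude toward controlling behaviour in objective 3, section 6.6.1 and section 6.17, and draw no conclusion about behaviour. An experience item could still be added at endline, but it would have no matching baseline and could be compared between arms only.

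**Separately**, replace item 212 in Annex III with the burnt-food scenario so that all versions carry the same five attitude items.

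The cost is one stem and one item, with re-translation and a place in the pre-test already planned. Sample size and the primary analysis do not change. Renaming costs only text, but gives up the behavioural part of objective 3.
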